## Abstract

**Background:**

Although screening for tobacco use is increasing with electronic health records and standard protocols, other tobacco-control activities, such as referral of patients to cessation resources, is quite low. In the QUIT-PRIMO study, an online referral portal will allow providers to enter smokers' email addresses into the system. Upon returning home, the smokers will receive automated emails providing education about tobacco cessation and encouragement to use the patient smoking cessation website (with interactive tools, educational resources, motivational email messages, secure messaging with a tobacco treatment specialist, and online support group).

**Methods:**

The informatics system will be evaluated in a comparative effectiveness trial of 160 community-based primary care practices, cluster-randomized at the practice level. In the QUIT-PRIMO intervention, patients will be provided a paper information-prescription referral and then "e-referred" to the system. In the comparison group, patients will receive only the paper-based information-prescription referral with the website address. Once patients go to the website, they are subsequently randomized within practices to either a standard patient smoking cessation website or an augmented version with access to a tobacco treatment specialist online, motivational emails, and an online support group. We will compare intervention and control practice participation (referral rates) and patient participation (proportion referred who go to the website). We will then compare the effectiveness of the standard and augmented patient websites.

**Discussion:**

Our goal is to evaluate an integrated informatics solution to increase access to web-delivered smoking cessation support. We will analyze the impact of this integrated system in terms of process (provider e-referral and patient login) and patient outcomes (six-month smoking cessation).

**Trial Registration:**

Web-delivered Provider Intervention for Tobacco Control (QUIT-PRIMO) - a randomized controlled trial: NCT00797628.

## Background

Tobacco use is the number one behavioral health problem and number one preventable cause of death [1-5]. Interventions to reduce smoking have most frequently targeted patients. Patient self-management interventions for smoking cessation include mass dissemination of tobacco cessation self-help materials, computer-tailored printouts, interactive voice response systems, and more recently, "quitlines" and smoking cessation websites [3,6-13]. Unfortunately, self-management interventions for smoking cessation have been underutilized. Studies of quitlines note that as little as 3.5% of adult smokers call per year [14]. Because the majority of smokers (70%) see a healthcare provider at least once per year [15], physician referrals could greatly increase use of publicly available self-management interventions for smoking.

Quality improvement and implementation interventions have tried to change processes of care or provider behavior related to tobacco control with some success. Brief clinical interventions, based on tobacco use screening and brief, structured cessation advice from a provider, have been documented to improve patient cessation rates [15-18]. The current US Department of Health and Human Services clinical practice guideline entitled "Treating Tobacco Use and Dependence" provides a summary of evidence-based recommendations [5]. The current guideline includes a framework for structured, brief clinical interventions using the "5 *A*s" of counseling:

1. Ask: Identify and document tobacco use status for every patient at every visit.

2. Advise: In a clear, strong, and personalized manner, urge every tobacco user to quit.

3. Assess: Is the tobacco user willing to make a quit attempt at this time?

4. Assist: Refer to resources and provide pharmacotherapy and counseling.

5. Arrange: Schedule follow-up contact, preferably within the first week after the quit date.

The first two *A*s (Ask and Advise) have increased through system-based interventions (*i.e*., smoking status as a vital sign) [19,20] and audit and feedback of smoking counseling performance [21,22]. However, implementation of Assist and Arrange has been lower [21,23,24]. One important component of assisting patients mentioned in the guideline is to refer patients to community resources, such as quitlines [15]. As quitlines and websites have proliferated, "Refer," as part of the Assist agenda, has been increasingly emphasized [25]. In practice, rates of referral to cessation resources have been measured to be as high as 28% at the VA [26] and 37% in managed care [27] and as low as 10% in community-based practices [28]. Providers do refer some patients to quitlines. In one study, 20% of quitline users were referred by providers [29]. Barriers to Refer include provider's lack of (a) time due to competing demands, (b) awareness of referral resources, (c) prompts, (d) materials to facilitate referrals, and (e) feedback on referral's success [30]. Both patient and provider barriers to using resources for smoking cessation could potentially be addressed with an integrated system.

In this report, we describe the protocol for the QUIT-PRIMO-quality improvement in tobacco-provider referrals and Internet-delivered microsystem optimization-provider-to-patient informatics system. The informatics system will allow providers at the point of care to use a simple web portal to "e-refer" patients to a smoking cessation website. Providers simply type the smokers' email into the ReferaSmoker. Patients will then receive motivational emails encouraging them to join the patient intervention website (with interactive tools, educational resources, motivational email messages, secure messaging with tobacco treatment specialists and an online support group). Providers will subsequently get reports of patient activity on the smoking cessation website.

Our overall goal is to advance science related to the use and impact of the Internet in health services delivery of tobacco control. Because the informatics system is designed to engage all providers in a primary care clinic, including physicians and nurses, we will evaluate the system in a cluster-randomized trial. We will randomize 160 primary care clinical microsystems to the intervention or comparison group. For both the intervention and comparison groups, we will adapt protocols used in prior successful Internet-delivered provider interventions to recruit practices and implement the system in practices [31,32]. Because our trial targets both practices and patients, patients within practices undergo a second level of randomization, as described below. We will use the discussion of our cluster-randomized trial to detail our approach to inherent measurement challenges in this randomized trial of a mixed provider-patient informatics intervention.

## Methods

### Study design

We will recruit 160 primary care physician practices to our trial. As further detailed below, our primary intervention target is the clinical practices. Patients nested within these practices will be cluster-randomized to receive either a simple paper referral or the full intervention-a paper referral plus an "e-referral" (smoker's email will be entered into a referral system and the smoker will receive encouraging emails to participate). In addition to our primary cluster-randomized trial, patients who participate in the website will be further randomized (patient-level, within-practice randomization) to receive either a standard or augmented patient website. Thus, our design is a randomized trial of a patient smoking cessation intervention, nested within a cluster-randomized practice intervention.

### Participants

Our target is the primary care clinical microsystem within family practice and general internal medicine practices from across the United States. A clinical microsystem is defined as the smallest functional healthcare unit. A clinical microsystem is not simply equivalent to a group of doctors, but includes the clinical team of nurses, the processes of care that are used, and the panel of patients cared for by the providers. The Institute for Healthcare Improvement states that interventions targeted to clinical microsystems are "a crucial component in improving health care quality." [33] Our informatics intervention targets both the practice staff and their patients, and thus, both practices and patients are described as participants.

#### Participating practices

Practices will be recruited using a database of registered internal medicine and family/general practitioners. Initial interest will be ascertained via mass mailing of an interest survey. Once initial interest is expressed by return of the brief interest survey, each practice will be assessed for inclusion.

We are including community-based primary care practices (general internal medicine and family practice). Exclusion criteria include those practices that do not have Internet access available to staff and practices that do not see at least five or more smokers in one week. In addition, we will selectively recruit practices that have five or less providers. Based on our prior experience, enrollment of practices in these studies is complex and is somewhat easier if the number of providers in the practice is lower. Thus, we will exclude practices that have greater than five physicians. We will also exclude practices with ongoing computer-based smoking cessation programs, and we will not recruit from practices participating in ongoing studies or similar prior studies, especially those focused on tobacco control.

#### Participating patients

Patients will be referred to an online smoking cessation system (Decide2Quit.org). Patients referred will be adult smokers in the intervention and comparison practices. Decide2Quit.org is designed as a cessation induction and support for quitting system, tailored to readiness to quit. Thus, we are including those ready to quit, thinking about quitting, or not thinking about quitting.

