#### ReferaSmoker.org, the practice-level intervention

Intervention practices will be provided preprinted pads of "information prescriptions" with their office information, a space for the provider to sign, and the smoking cessation website address (Decide2Quit.org). The information prescriptions are perforated; half will be retained by the practice (including the patient email to be used for e-referral) and half will be provided to the patient (see Additional File 1, Appendix 1). Practices will then use this patient email collection to e-refer them through ReferaSmoker.org. The core of the ReferaSmoker.org provider portal is a secure sockets layer (SSL) encrypted web form where providers can enter patients' email addresses into the system if they agree to be referred (Figure 1). The form has been designed to be easily completed by nursing or front office staff as the patient is discharged from the visit. Online referrals through the SSL form will be tracked by the server. The practice-reports function will provide feedback reports to providers on their patients' progress and their practice's referral rates. These feedback reports will act as a proximal outcome, where providers of all types can actually observe the impact of their efforts. To maximize the use of ReferaSmoker.org, we also provide supportive sub modules designed to prompt providers to use the system and maximize their smoking cessation activities (Figure 1, ReferaSmoker #3).

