#### The practice-level comparison

The practice-comparison referral process ends at the information prescriptions. Comparison practices will be enrolled in the same manner and will participate in the implementation program training calls. Randomization will occur on the calls once registration is complete, as further described below. The ReferaSmoker.org portal changes dynamically based on the randomization status of the practice, and comparison practices will only receive the supportive educational materials (Figure 1, ReferaSmoker #3). Comparison practices do not have access to the e-referral system, the practice feedback dashboard, or the secure messaging system.

As noted, comparison practices are provided preprinted pads of information prescriptions, exactly like those the intervention practice received, save one detail. There is no space for the patient email because control providers will not use the e-referral system (see Additional File 2, Appendix 2). Smokers will be provided half the information prescriptions, with the Decide2Quit.org address, just as with the intervention practices. All other components of the implementation program, motivational interviewing and goal-setting, incentives, and booster calls are kept constant across the two arms. Practices randomized to the comparison do receive a more limited training, focusing on the paper information prescriptions.

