### Outcomes

For our three hypotheses, we have three primary outcome variables (*i.e*., Refer, Go, Quit). For the primary analysis for hypothesis 1, the outcome will be the number of smokers referred from each group transformed into an average count per month by dividing the total by the length of time in months from the practice's first referral. As discussed above, in both arms, practices will use paper information prescriptions. The leave-behind part of the information prescription (see Appendix 1) will allow a consistent measure of referrals. In the QUIT-PRIMO intervention, the server will track the number of electronic referrals, allowing us to compare rates of referral based on paper and server in the intervention arm.

For hypothesis 2, our outcome will be the proportion of those referred who go to the website. Our interest in hypothesis 2, expressed as a proportion, will be the proportion of patients referred who log on, or "Go," to the website (% who go = number who visit/number referred). The number of smokers who visit will be recorded by the Decide2Quit system, linking each visitor to their primary care provider at initial registration. The number referred is continuously registered directly by the leave-behind referral receipts of the information prescriptions.

For hypothesis 3, we will define the outcome in two ways. In both approaches, the numerator will be the number of patients who report cessation at six-month follow-up calls. In our primary intent-to-treat analysis, the denominator will be all smokers who are referred (the same denominator used in hypothesis 2), estimating a population effect. This represents a conservative assessment since we assume that many patients will not go, and for the purposes of analyses, we will assume that these patients will not have quit. As a secondary analysis, we will assign the denominator as the number of patients who go to the website. For this secondary outcome, consistent with current guidelines for smoking cessation trials, we will assume that patients who are lost to follow-up, including those who go and do not agree to follow-up, are smokers [34].

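### Only the intervention pad asks for an email, on the slip that forms the Go denominator, so uneven slip completion for smokers without email could bias the Go comparison

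*Protocol article*

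**What the plan says.** Under Participating practices, Internet access is asked of the practice: "Exclusion criteria include those practices that do not have Internet access available to staff". Under Participating patients, the criterion is adult smoking at any readiness to quit: "Patients referred will be adult smokers in the intervention and comparison practices". Nothing is asked about the patient's own email or Internet access.

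The practice-level intervention adds e-referral to a paper prescription. On the perforated intervention pad, "half will be retained by the practice (including the patient email to be used for e-referral"), and the portal is a form "where providers can enter patients' email addresses into the system if they agree to be referred". The comparison pad differs in one respect: "There is no space for the patient email because control providers will not use the e-referral system".

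Under Outcomes, Go is a ratio, "who go = number who visit/number referred". The number referred is taken from the retained paper slips in both arms, which the article regards as a consistent measure. The server count of e-referrals is a separate figure, for comparing paper with electronic referral inside the intervention arm. Under Analysis, Go is modelled at patient level with a logit link and GEE for clustering by practice. No measure of patient access is named.

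**The concern.** The only stated difference between the two pads is an email line, and it sits on the form that defines who is in the Go denominator. That denominator forms after randomization, through staff who know which referral process they use, even though the article describes practices as blind to group assignment. In the intervention arm, the e-referral step cannot be done for a smoker without email. Staff may then skip the slip for some of these smokers, while comparison staff have no such prompt.

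If that happens, the intervention denominator holds a larger share of smokers who can reach the site, and its Go rate rises even if e-referral does nothing. The hypothesis 1 count moves the other way, because the intervention arm loses slips that the comparison arm keeps. GEE allows for correlation within practices; it does not correct a difference between arms in who was entered.

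**Working it through.** **The plan's own figures (Sample size, Table 2).**
- Smokers: 3,000 × 0.22 = 660.
- Intervention: 660 × 0.24 = 158.4 referred; × 0.40 = 63.4 go.
- Control: 660 × 0.12 = 79.2 referred; × 0.20 = 15.8 go.

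These agree with the table's 158 and 63, and 79 and 16. The planned Go difference is 40% − 20% = 20 points.

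**Model with no true effect of e-referral.** Let a be the share of smokers with access, and f the share of smokers without access who get no counted slip in the intervention arm. All such smokers are counted in the comparison arm, and none of them can go. Neither a nor f is in the documents; both are assumptions. With comparison Go fixed at the planned 20%:

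intervention Go = 0.20 / [a + (1 − a)(1 − f)]

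| a | f | Intervention Go | False difference |
|---|---|---|---|
| 0.60 | 1 | 0.20/0.60 = 33.3% | 13.3 points |
| 0.70 | 1 | 0.20/0.70 = 28.6% | 8.6 points |
| 0.80 | 1 | 0.20/0.80 = 25.0% | 5.0 points |
| 0.90 | 1 | 0.20/0.90 = 22.2% | 2.2 points |
| 0.80 | 0.5 | 0.20/0.90 = 22.2% | 2.2 points |
| any | 0 | 0.20/1 = 20.0% | 0 |

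The rows with f = 1 are upper bounds for each access share. The whole planned 20 points would need a = 0.50 and f = 1 (0.20/0.50 = 40%).

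**Chance of a false significant Go result.** Further assumptions: 80 practices per arm, two-sided alpha 0.05, and patient numbers of 80 × 158 and 80 × 79, each divided by 1 + (m − 1) × ICC. The planned 158 is kept although some slips would be lost.
- a = 0.80, f = 0.5: 69%, 29% and 18% at ICC 0.01, 0.05 and 0.10.
- a = 0.80, f = 1: about 100%, 88% and 63%.

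So an artefact that is small beside 20 points can still raise the type I error well above 5%.

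**Hypothesis 1.** Intervention referrals fall by the fraction (1 − a)f. At a = 0.80, f = 0.5 this is 10%, or 158 × 0.90 = 142 per practice. At a = 0.70, f = 1 it is 30%, or 158 × 0.70 = 111. Both assume that the 24% referral rate in Table 2 made no allowance for access, which the article does not say.

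**Hypothesis 3.** Patients are randomized to a website version within practice, after they register online. A smoker who cannot reach the site never gets that far. In the all-referred denominator such smokers lower the quit rate, but the pad difference is not the contrast under test.

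**The case against.** The strongest reply is that the protocol already defines a referral as a paper slip, in both arms. Email is needed for the e-referral, not for being counted. An intervention smoker without email who receives a slip enters the denominator exactly as in a comparison practice. No section says that such a smoker is refused a slip or left out. The stated incentives also favour completing slips: practices set referral goals, and the $1,000 budget depends on training and the first 20 referred smokers, with incentives held constant across arms. Finally, this is a journal article; the pads are in additional files that are not shown, and the handling of a blank email line may be in the full protocol.

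Most of this stands. A reader might infer that the email line creates an access criterion in one arm only. The documents do not support that: no such criterion is stated, and with f = 0 the artefact is zero. A reader might also infer that hypothesis 3 is biased between its arms. It is not, because website randomization follows registration. Nor is it an error to count all referred smokers for hypothesis 3; the article presents that as a deliberate population-effect choice.

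What remains is narrower. The article calls the slip a consistent measure but describes a form that is not the same in the two arms, and its portal text links agreeing to be referred with giving an email. It nowhere says that a slip without an email is completed and counted. The common incentives make a large f less likely, but they do not fix it at zero. Only intervention practices have a dashboard of patient progress, which gives their staff more reason to attend to patients who can be e-referred.

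**Conclusion.** The point holds as a conditional bias in a primary outcome. If intervention staff complete fewer slips for smokers without email, Go is biased toward e-referral and the hypothesis 1 count against it. If every slip is completed and counted regardless of email, there is no between-arm bias. The size rests on two shares that the documents do not give: at most 13, 9 or 2 points for 60%, 70% or 90% access under complete one-arm exclusion, and about 2 points for 80% access with half excluded. It would account for the full planned difference only in the extreme case of 50% access and complete exclusion. It merits a change because a small artefact could still be declared significant, the planned model would not remove it, and access not recorded at the visit is unlikely to be recoverable for smokers who never register.

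**What to change.** - Print the same yes/no question on email or Internet access on the retained slip of both pads, to be answered before the referral step.
- State that a slip is completed and counted for every referred adult smoker in both arms, whether or not an email is given.
- Analyse Go among smokers answering yes in both arms, alongside Go among all referred, and report the number answering no by arm.
- Keep the stated denominators for hypotheses 1 and 3. Restricting them to smokers with access would change what those hypotheses estimate.

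Under the model above with a = 0.80 and f = 0.5, Go among those with access would be 0.20/0.80 = 25% in both arms, so the artefact disappears. The selection would also be visible: 20% of comparison slips would answer no, against 0.10/0.90 = 11% of intervention slips.

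The cost is one printed line per pad and a few sentences of text. The access-restricted Go result applies only to smokers with access and uses fewer referrals. Because the answer is collected after randomization, by staff who know their referral process, it reduces selection without fully removing it.

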### Interventions

Our discussion of the interventions begins with a comparison of the practice-level intervention.

#### ReferaSmoker.org, the practice-level intervention

Intervention practices will be provided preprinted pads of "information prescriptions" with their office information, a space for the provider to sign, and the smoking cessation website address (Decide2Quit.org). The information prescriptions are perforated; half will be retained by the practice (including the patient email to be used for e-referral) and half will be provided to the patient (see Additional File 1, Appendix 1). Practices will then use this patient email collection to e-refer them through ReferaSmoker.org. The core of the ReferaSmoker.org provider portal is a secure sockets layer (SSL) encrypted web form where providers can enter patients' email addresses into the system if they agree to be referred (Figure 1). The form has been designed to be easily completed by nursing or front office staff as the patient is discharged from the visit. Online referrals through the SSL form will be tracked by the server. The practice-reports function will provide feedback reports to providers on their patients' progress and their practice's referral rates. These feedback reports will act as a proximal outcome, where providers of all types can actually observe the impact of their efforts. To maximize the use of ReferaSmoker.org, we also provide supportive sub modules designed to prompt providers to use the system and maximize their smoking cessation activities (Figure 1, ReferaSmoker #3).

